### Design

This is a double-blind, randomized, controlled, 2-period, crossover trial comparing melatonin to placebo in adults with chronic neuropathic pain (Figure 1). Both treatment periods will be 5 weeks in duration, and the entire trial will be 10 weeks long for each participant. Participants will be randomized to one of the two treatment sequences. The randomization sequence will be generated using the web-based program randomization.com (Dallal, Tufts University). Participants in sequence 1 will take active melatonin capsules during the first 4 weeks of the trial (followed by a 1-week washout period) and will subsequently take inert placebo capsules for the next 4 weeks of the trial (followed by a 1-week washout period). Participants in sequence 2 will take inert placebo capsules during the first 4 weeks of the trial (followed by a 1-week washout period) and will subsequently take active melatonin capsules for the next 4 weeks of the trial (followed by a 1-week washout period). Figure 1 shows a schematic representation of the trial design.

**Figure 1 figure1:**
[figure not shown]
Clinical Trial Schema.

### Setting

Investigators work at a tertiary care health sciences center (Providence Care Hospital) in Kingston, Ontario, Canada.

### Participants

Men and women meeting the diagnostic criteria for peripheral NP will be considered for recruitment following informed consent. The inclusion criteria are as follows: (1) a score of 4 or higher on the DN4 interview—a validated questionnaire that distinguishes between neuropathic and nonneuropathic pain [24]; as indicated, investigations will be performed to confirm an NP diagnosis including, but not limited to, nerve conduction studies and electromyography; (2) daily pain (score of ≥4/10) for at least 3 months; (3) alanine transaminase level≤120% of the upper normal limit; (4) creatinine clearance of ≥60 mL/min; (5) glycosylated hemoglobin of ≤9.5%; and (6) necessary abilities, visual acuity, and language skills for questionnaire completion and telephone communication with nurses. The exclusion criteria are as follows: (1) major organ system disease; (2) cardiovascular autonomic neuropathy; (3) trigeminal neuralgia, complex regional pain syndrome, or central NP; (4) moderate to severe sedation or ataxia due to other required concomitant drugs; (5) allergy or hypersensitivity to study medications or any components in the study drug formulations or its containers; (6) seizure disorder; (7) other painful conditions that are >50% as severe as their NP; (8) a major, poorly controlled psychiatric disorder, depression or suicidal ideation, or active substance use disorder; (9) candidates who live alone and cannot assure daily contact with a friend, family member, or caregiver; (10) women of childbearing potential who will not receive a highly effective form of contraception (total abstinence, hormonal birth control methods, intrauterine devices, confirmed successful vasectomy of the partner, double barrier methods such as condom or diaphragm, etc) or a positive pregnancy test at baseline (If a study participant becomes pregnant, she must stop using study medications immediately and will be withdrawn from the study); (11) women who are breastfeeding or who plan to breastfeed; (12) regular daily administration of opioids at a dose greater than 90 mg morphine equivalents; and (13) lack of a primary care physician.

### Randomization and Blinding

We will use a balanced Latin Square crossover design [25-27] in which participants will be allocated to one of the two treatment sequences: melatonin and placebo. At the beginning of the trial, an investigational pharmacist will use a computer-generated randomization process to prepare a concealed allocation schedule to randomly assign the treatment sequences in appropriate block sizes to a consecutive series of numbers. On enrollment, each participant will be assigned to the next consecutive number, and the corresponding series of study medications will be dispensed (eg, melatonin followed by placebo or placebo followed by melatonin). Study medications will be formulated in an identical fashion across treatment periods. Treatment codes for each study participant will be generated by an investigational pharmacist and will not be disclosed to study personnel or participants until completion of the trial. Study outcome measures will be evaluated and recorded by the research study nurse who will be blinded (as will the rest of the research team) to treatment group assignments until trial completion. As an assessment of blinding to the treatment group, each participant and the study nurse will complete a blinding questionnaire at the end of each treatment period.

### Cointerventions and Rescue Medication

Any enrolled participants already taking melatonin will be weaned off during a pretrial washout of at least 7 days. Participants taking and perceiving benefit from opioids (<90 mg morphine equivalents), antidepressants (tricyclic, selective serotonin reuptake inhibitor, or serotonin-norepinephrine reuptake inhibitor), nonsteroidal anti-inflammatory drugs, or acetaminophen may continue these medications at a steady daily dose for the duration of the study. Any ongoing cognitive behavioral therapy or exercise programs perceived as beneficial will be allowed to continue only if it is certain that these will be evenly used throughout the trial. Participants will not be allowed to start new medications, cognitive-behavioral therapy, or exercise programs at any point during the study. Participants will be required to avoid any procedural pain therapies (eg, neurosurgical interventions, nerve blocks, or acupuncture) during the study. Participants will be permitted to take acetaminophen (≤8 tablets, 325 mg/tablet daily) for inadequate pain relief only during the taper and washout phases of each treatment period. Acetaminophen consumption will be recorded as a secondary outcome measure.

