### Study Treatment Dosing Schedule

During each period of this trial, participants will receive 1 set of capsules (melatonin capsules, Bio-tech Pharmacal) containing 3 mg melatonin or placebo (lactose capsules). Each period will last 5 weeks, with a 4-week treatment period and a 1-week washout period. During week 1 of each treatment period, participants will take 1 capsule before bedtime. During week 2, participants will take 2 capsules before bedtime. During week 3 participants will take 3 capsules before bedtime, and during week 4, participants will take 4 capsules before bedtime. The ceiling dose for melatonin is 12 mg/day. With each increase in the dosage of study medication in the titration schedule, if mild to moderate treatment-emergent AEs (eg, sedation) are encountered, participants will be asked if they can tolerate continuing at that dose for another 2-3 days. If so, this dosage will be continued with the expectation that tolerance to side effects will occur. If side effects are severe, intolerable, or do not improve, both study medications will be decreased to the next lowest possible dose and an increase will be attempted one more time at the next scheduled dose increase. If this again results in intolerable side effects, both study drugs will be decreased back to the previous dose, which will be defined as the maximal tolerated dose (MTD) for that individual. However, during this flexible dose titration, the final dose arrived at during the MTD week (week 4 of the treatment period) could be lower than the ceiling dose of 12 mg if side effects encountered during the dose titration (eg, excessive sedation) are suspected to be due to melatonin.

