### Outcome Measures

During the trial, the study nurse will contact participants by telephone at least once a week to evaluate adverse effects, assess pain intensity, and encourage compliance. Furthermore, participants will be evaluated at the clinic on 1 of the 5 weekdays of week 4 of each treatment period for vital signs and assessment of secondary outcomes. Finally, participants will be followed up by telephone 2 weeks and 3 months following the completion of the study to document any subsequent problems or adverse events. Table 1 shows the schedule of study assessments.

The primary outcome is the mean daily “average” pain intensity [28] experienced while on the MTD of melatonin or placebo during week 4 (days 22-28). This will be determined from participants’ ratings of their “average pain over the last 24 hours” completed in patient diaries every morning using a numerical rating scale from 0 to 10. Given the potential circadian variability of pain intensity [29], clinical trial methods have involved the following: (1) requiring participants to rate their pain multiple times through the day or evening [26,27], which increases participant burden and may adversely affect participant retention or missing data or (2) requiring participants to provide a retrospective rating of their “average pain over the last 24 hours” [30], which may be susceptible to recency bias. Based on our experience, we are proposing the latter approach, although both approaches have led to valid and generalizable trial results in clinical pain trials. Secondary outcomes include frequency or severity of treatment-emergent AEs; scores on the Neuropathic Pain Symptom Inventory [31], Medical Outcomes Study Sleep Scale [32], Patient Global Impression of Change [33], Brief Pain Inventory [34], Beck Depression Inventory-II [35], Beck Anxiety Inventory [36], the short-form McGill Pain Questionnaire [37], the SF-36 survey [38], and blinding questionnaires; and acetaminophen consumption. All these outcomes will be assessed at baseline and during week 4 of each treatment period, except for AEs and acetaminophen consumption, which will be assessed weekly during each treatment period.

**Table 1 table1:** Schedule of study assessments.

Assessments	Screen	Baseline	treatment periods				3-month posttrial completion
			First 3 weeks of treatment	Fourth week of treatment	Washout		
Days per treatment period >	–14	–7	1-21	22-28	29-35		
Present pain intensity (scale 0-10; average and worst)	✓						

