Concurrent medications^a^	✓	✓	✓	✓	✓	✓	
Demographics and medical history	✓						
Vital signs and weight	✓			✓			
Clinical laboratories	✓						
Adverse events^a^	✓	✓	✓	✓	✓	✓	
Drug dispensing		✓		✓			
Drug compliance and accountability				✓			
Daily pain diaries		✓	✓	✓	✓		
Maximum tolerated dose levels			✓	✓	✓		
Medical Outcomes Study Sleep Scale		✓		✓			
Other adverse effects^a^			✓	✓	✓		
Patient global impression of change			✓	✓	✓		
Brief Pain Inventory		✓		✓			
Beck Depression Inventory–II	✓	✓		✓			
Medical Outcomes Study 36­item short­form health survey		✓		✓			
Rescue acetaminophen^a^			✓	✓	✓		
Blinding questionnaire				✓			
Neuropathic Pain Symptom Inventory		✓		✓			
Pregnancy test for women of childbearing potential	✓						

^a^Evaluated during weekly participant telephone contacts with the research nurse.

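### Rescue acetaminophen is allowed only in a taper that the schedule does not contain and in washout, so its consumption, a secondary outcome, cannot show a treatment effect at the maximally tolerated dose

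*Protocol article*

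**What the plan says.** **Rescue rule.** Cointerventions and Rescue Medication permits up to 8 tablets of 325 mg acetaminophen daily "for inadequate pain relief only during the taper and washout phases of each treatment period". The next sentence reads "Acetaminophen consumption will be recorded as a secondary outcome measure".

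**Background use.** The same section lets participants who already benefit from certain analgesics continue them. The list ends "or acetaminophen may continue these medications at a steady daily dose for the duration of the study".

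**Schedule.** Study Treatment Dosing Schedule states "Each period will last 5 weeks, with a 4-week treatment period and a 1-week washout period". The scheduled dose rises by one capsule a week, and "during week 4, participants will take 4 capsules before bedtime". Design gives the same structure of four weeks of capsules and one week of washout, twice. Neither section describes a taper.

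**Collection.** Outcome Measures assesses the secondary outcomes at baseline and in week 4, "except for AEs and acetaminophen consumption, which will be assessed weekly during each treatment period". In Table 1 the row "Rescue acetaminophen^a" is ticked for days 1-21, days 22-28 and washout (days 29-35), and its footnote ties it to the weekly nurse calls.

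**Analysis.** Statistical Analysis has the secondary outcomes analysed like the primary outcome, which is a week-4 measure compared by a linear mixed model.

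**The concern.** An outcome meant to compare rescue use between treatments is informative only where participants are free to take rescue. Here one section bars it outside two named phases, one of those phases does not exist in the schedule, and other sections collect it as an outcome in every week. A reader cannot tell in which weeks a recorded tablet is an outcome event and in which it is a protocol deviation.

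The stake is interpretation. If week-4 consumption goes through the same model as the primary outcome, the model is fitted to deviations. If washout consumption is used, the contrast describes days on which no study capsule is taken. In either case a null result could be reported as showing that melatonin does not reduce the need for other analgesics, when the design gave it no opportunity to do so at the dose of interest.

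**Working it through.** The plan states no figure for this outcome, so there is none to reproduce. The check sets the rescue rule against the schedule and counts days.

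**Inputs**
- Length of a period: 4 treatment weeks + 1 washout week = 28 + 7 = 35 days (Study Treatment Dosing Schedule; Table 1).
- Week 4, days 22-28: the week at the maximally tolerated dose and the primary-outcome window (Outcome Measures).
- Rescue permitted: taper and washout only (Cointerventions and Rescue Medication).
- Position and length of the taper: not given, so each possible reading is tried.

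**Formula:** barred days = 35 − washout days − taper days.

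| Reading of taper | Permitted days | Barred days | Permitted use in week 4 | Fit with the text |
|---|---|---|---|---|
| No taper, as the schedule reads | 29-35 | 35 − 7 − 0 = 28 | none | Leaves the word without a meaning |
| Lies inside days 29-35 | 29-35 | 28 | none | Shortens the stated one-week washout |
| Means the titration weeks 1-3 | 1-21 and 29-35 | 35 − 7 − 21 = 7 | none | Not stated; doses rise in these weeks |
| Lies in week 4 | some or all of 22-28, and 29-35 | 28 − taper days (21 to 27) | some | Contradicts the week-4 dosing; opens the primary window to rescue |

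**Consequences**
1. In the first three readings, permitted rescue in week 4 is 0 tablets under melatonin and 0 under placebo. The permitted contrast at the maximally tolerated dose is 0 − 0 = 0 by rule, and any non-zero value is a deviation.
2. In the first two readings, the only permitted use (up to 8 × 325 = 2600 mg a day) falls on days 29-35, when no capsules are scheduled. That is off-drug use.
3. In the titration reading there is an on-drug contrast in weeks 1-3, at scheduled doses of 1 to 3 capsules (3 to 9 mg), but none in week 4.
4. Only the fourth reading gives a permitted contrast in week 4, and it conflicts with the dosing schedule.

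**Background use.** The text names the outcome acetaminophen consumption; Table 1 names it rescue acetaminophen. These differ for anyone who continues background acetaminophen. If background use is counted, it is held steady by rule, so it adds a constant and carries no treatment effect.

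**The case against.** Several objections have force.

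- **Table 1 grants no permission.** It is a schedule of assessments. Asking about rescue in weeks when it is barred is a sensible way to detect unpermitted use. This stands, and it justifies the collection. It does not make the collected quantity an outcome, which is what two sections call it.
- **Washout is covered.** Design describes each treatment period as five weeks, and Table 1 ticks the washout column, so weekly assessment includes days when rescue is allowed. This also stands, but those days are off drug.
- **Taper may loosely mean titration.** Rescue would then be barred only in week 4. The text does not say so, but it cannot be excluded. A reader might infer that on-treatment use is zero by rule for 28 of 35 days. That figure assumes a taper of zero length, and the documents support only a range of 7 to 28.
- **The primary outcome is protected.** A reader might infer that rescue use contaminates the week-4 pain scores. If the rescue rule is followed with no taper in week 4, rescue is kept out of that window; contamination would need a violation. Barring rescue there can be a sound choice and is not disputed here.
- **Washout pain.** A reader might also infer a bias from comparing washout pain, with rescue allowed, with week-4 pain. No such comparison is planned.
- **An article leaves detail to the full protocol.** True for an exact outcome window. Here, however, a stated rule, a stated schedule and a stated outcome do not fit together, which is a conflict and not an omission.

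**Conclusion.** The point holds in limited form. The rescue rule names a phase that the schedule lacks, and the secondary outcome is collected across weeks in which its use is barred, in whole or in part. The barred time is between 7 and 28 of 35 days per period, depending on what taper means. On every reading except a taper in week 4, which contradicts the dosing schedule, permitted use at the maximally tolerated dose is zero in both treatments. On the narrowest reading, all permitted use is off drug. The outcome therefore cannot show a treatment effect on analgesic need at that dose.

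This assumes that the rescue rule is followed and that analysing the outcome like the primary one means using week 4. The titration reading leaves a usable contrast in weeks 1-3, so the outcome is not necessarily empty throughout treatment. The primary analysis and the sample size do not depend on this point. It should be corrected because it concerns a named outcome and is cheap to settle.

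**What to change.** **Reconcile the text.** Cointerventions and Rescue Medication, Study Treatment Dosing Schedule, Outcome Measures and Table 1 should agree on three things: whether a taper exists and on which days, in which weeks rescue is permitted, and whether continued background acetaminophen counts towards the outcome. Which clinical rule applies is for the investigators.

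**Then match the outcome to the rule.**
- If rescue is not permitted on treatment: drop consumption as a comparative outcome, keep the weekly question, record on-treatment use as a deviation, and report washout use descriptively as off-drug use.
- If rescue is permitted in some treatment weeks: define the outcome on those weeks only.
- If those weeks include week 4: also add a sensitivity analysis of the primary outcome that takes account of rescue use.

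**Cost.** A few sentences of protocol text and one outcome definition. No extra data are needed, since the weekly calls already collect rescue use. At most, one uninformative secondary comparison is lost.

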### Study Treatment Dosing Schedule

During each period of this trial, participants will receive 1 set of capsules (melatonin capsules, Bio-tech Pharmacal) containing 3 mg melatonin or placebo (lactose capsules). Each period will last 5 weeks, with a 4-week treatment period and a 1-week washout period. During week 1 of each treatment period, participants will take 1 capsule before bedtime. During week 2, participants will take 2 capsules before bedtime. During week 3 participants will take 3 capsules before bedtime, and during week 4, participants will take 4 capsules before bedtime. The ceiling dose for melatonin is 12 mg/day. With each increase in the dosage of study medication in the titration schedule, if mild to moderate treatment-emergent AEs (eg, sedation) are encountered, participants will be asked if they can tolerate continuing at that dose for another 2-3 days. If so, this dosage will be continued with the expectation that tolerance to side effects will occur. If side effects are severe, intolerable, or do not improve, both study medications will be decreased to the next lowest possible dose and an increase will be attempted one more time at the next scheduled dose increase. If this again results in intolerable side effects, both study drugs will be decreased back to the previous dose, which will be defined as the maximal tolerated dose (MTD) for that individual. However, during this flexible dose titration, the final dose arrived at during the MTD week (week 4 of the treatment period) could be lower than the ceiling dose of 12 mg if side effects encountered during the dose titration (eg, excessive sedation) are suspected to be due to melatonin.

### Outcome Measures

During the trial, the study nurse will contact participants by telephone at least once a week to evaluate adverse effects, assess pain intensity, and encourage compliance. Furthermore, participants will be evaluated at the clinic on 1 of the 5 weekdays of week 4 of each treatment period for vital signs and assessment of secondary outcomes. Finally, participants will be followed up by telephone 2 weeks and 3 months following the completion of the study to document any subsequent problems or adverse events. Table 1 shows the schedule of study assessments.

The primary outcome is the mean daily “average” pain intensity [28] experienced while on the MTD of melatonin or placebo during week 4 (days 22-28). This will be determined from participants’ ratings of their “average pain over the last 24 hours” completed in patient diaries every morning using a numerical rating scale from 0 to 10. Given the potential circadian variability of pain intensity [29], clinical trial methods have involved the following: (1) requiring participants to rate their pain multiple times through the day or evening [26,27], which increases participant burden and may adversely affect participant retention or missing data or (2) requiring participants to provide a retrospective rating of their “average pain over the last 24 hours” [30], which may be susceptible to recency bias. Based on our experience, we are proposing the latter approach, although both approaches have led to valid and generalizable trial results in clinical pain trials. Secondary outcomes include frequency or severity of treatment-emergent AEs; scores on the Neuropathic Pain Symptom Inventory [31], Medical Outcomes Study Sleep Scale [32], Patient Global Impression of Change [33], Brief Pain Inventory [34], Beck Depression Inventory-II [35], Beck Anxiety Inventory [36], the short-form McGill Pain Questionnaire [37], the SF-36 survey [38], and blinding questionnaires; and acetaminophen consumption. All these outcomes will be assessed at baseline and during week 4 of each treatment period, except for AEs and acetaminophen consumption, which will be assessed weekly during each treatment period.

**Table 1 table1:** Schedule of study assessments.

Assessments	Screen	Baseline	treatment periods				3-month posttrial completion
			First 3 weeks of treatment	Fourth week of treatment	Washout		
Days per treatment period >	–14	–7	1-21	22-28	29-35		
Present pain intensity (scale 0-10; average and worst)	✓						
Concurrent medications^a^	✓	✓	✓	✓	✓	✓	
Demographics and medical history	✓						
Vital signs and weight	✓			✓			
Clinical laboratories	✓						
Adverse events^a^	✓	✓	✓	✓	✓	✓	
Drug dispensing		✓		✓			
Drug compliance and accountability				✓			
Daily pain diaries		✓	✓	✓	✓		
Maximum tolerated dose levels			✓	✓	✓		
Medical Outcomes Study Sleep Scale		✓		✓			
Other adverse effects^a^			✓	✓	✓		
Patient global impression of change			✓	✓	✓		
Brief Pain Inventory		✓		✓			
Beck Depression Inventory–II	✓	✓		✓			
Medical Outcomes Study 36­item short­form health survey		✓		✓			
Rescue acetaminophen^a^			✓	✓	✓		
Blinding questionnaire				✓			
Neuropathic Pain Symptom Inventory		✓		✓			
Pregnancy test for women of childbearing potential	✓						

^a^Evaluated during weekly participant telephone contacts with the research nurse.

